### Sample size estimation

The study will recruit 319 sick children per cluster and the total number of sick children to be recruited from all clusters will be 8910; adjusting for a 10 % loss to follow up and possible withdrawal of private outlets. This was based on assumption that the intervention will increase the primary outcome from 28 to 40 %, at a study power of 80 %, 5 % level of significance and a cluster correlation k, of 0.15; 20 clusters will be required. Ten (10) of them will be randomly allocated to the intervention and 10 to the control arm.

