**Methods/Design:**

A cluster randomized design will be applied to test the intervention in Mukono District, central Uganda. A sample of study clusters will implement the intervention. The intervention will consist of three components: i) raising awareness in the community: village health teams will discuss the importance of referral and encourage households to save money, ii) training and supervision of providers in the private sector to diagnose, treat and refer sick children, iii) regular meetings between the public and private providers (convened by the district health team) to discuss the referral system. Twenty clusters will be included in the study, randomized in the ratio of 1:1. A minimum of 319 sick children per cluster and the total number of sick children to be recruited from all clusters will be 8910; adjusting for a 10 % loss to follow up and possible withdrawal of private outlets.

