## Background

About half of mortality in children under five years of age in sub-Saharan Africa is caused by malaria, pneumonia and diarrhea [1]. Almost 60 % of parents with febrile children in Uganda first seek care in the private sector, especially at drug shops [2], however they provide sub-standard care [3, 4]. A functioning referral system is a critical part of an appropriate health care delivery system [5]. Referral systems have been given particular emphasis in the integrated community case management (iCCM), which is the recommended strategy for management of childhood illness in Africa [6]. In many developing countries, referral is an essential part of preventing unnecessary deaths: primary health care workers should refer children with life threatening illnesses which they are unable to treat properly [7]. In Uganda, the Ministry of Health encourages referrals from dispensaries and health centres to district hospitals, from district hospitals to regional and the National Referral hospitals [8]. Uganda’s under-five mortality is high, currently estimated at 66/1000 live births [9]. Low referral rates of sick children is one of the contributory factors [7, 8], particularly in those who seek care from the private sector.

Previous research in Uganda and elsewhere in Africa has found that referral rates of sick children from lower levels to higher levels of care are extremely low [7, 10–13]. Several factors have been attributed to poor referral rates including; lack of money and high costs involved in referral, long distances to the referral health facilities, poor attitudes of health workers, lack of drugs at the referral health facilities, lack of involvement of fathers in the referral process and waiting for malaria drugs provided at the lower level of care to finish [7, 11, 13, 14]. We propose an intervention designed to strengthen referral from private providers to higher level facilities with the aim of improving child survival by getting sick children to an appropriate level of care in a timely manner. The study targets children aged less than five years, especially in rural areas who have poor access to health interventions. The proposed intervention aims to improve uptake of referral advice for children that seek care from private facilities (registered drug shops/private clinics). We describe the trial management structure, interventions, design, and analysis plan, as well as expected contributions that this study can make.

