## Study outcomes and analytic methods

The primary analytic approach is intention to treat with children in the clusters in the intervention arm considered exposed to the intervention. Data for all of the primary and secondary outcome variables will be captured on the routine treatment recording forms and all consultations for fever, pneumonia and diarrhea routinely completed by drug shop vendors/private clinics. The outcome of referral will be recorded on the referral forms by health staff for referred sick children presenting to health facilities with a referral form. The primary trial outcome is the proportion of sick children referred from a private outlet that complete referral (seen at higher level facilities). The denominator includes all referrals of sick children with a history of fever, pneumonia and diarrhoea. Through review of records at the private health facilities, care takers whose children are referred in a specific period of time will be followed up in their respective communities to verify whether they took up referral. Secondary outcomes are; appropriate case management for malaria, pneumonia and diarrhea among children and factors which influence referral or non-referral of sick children from the private sector. Other outcomes include the proportion of sick children seeking care at private outlets within 24 h of onset of symptoms, and time between consultations at private outlets and uptake of referral at health facilities (referral facilities).

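### The sample size counts sick children, but the primary outcome counts only referred children, so the stated 80% power does not follow from 319 per cluster

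*Protocol article*

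**What the plan says.** The Sample size estimation section gives the target in children attending the outlets: "The study will recruit 319 sick children per cluster". The abstract words this figure as "A minimum of 319 sick children per cluster". The overall total is put at 8910, which is said to allow for 10% loss and for outlets that drop out. The basis is that "the intervention will increase the primary outcome from 28 to 40" per cent, with 80% power at the 5% level and a quantity k of 0.15 that the section labels a cluster correlation. From this the article concludes that 20 clusters are needed, 10 per arm.

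Study outcomes and analytic methods defines the primary outcome as the proportion of referred children who are seen at a higher-level facility, and adds: "The denominator includes all referrals of sick children with a history of fever, pneumonia and diarrhoea". The outcome list beside Table 2 repeats the definition. The patient inclusion criteria admit any child under 5 with fever, cough or diarrhoea (or a raised temperature), referred or not. The analysis section uses k for the coefficient of variation.

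The article gives no expected share of sick children who will be referred. The Background says only that "referral rates of sick children from lower levels to higher levels of care are extremely low".

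**The concern.** The power claim is about one population (referred children) and the recruitment target about a larger one (all eligible sick children). The article gives nothing to convert one into the other. Two readings are possible, and the printed figures do not fit together on either. If 319 is meant as the outcome denominator, the stated inputs do not lead to 20 clusters. If 319 is meant as consultations, as written, the 80% depends on a referral share that is not stated.

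What is at stake is whether the stated power describes the trial. Progress judged against 319 sick children per cluster says little about the precision of the primary comparison, which depends on the number of referrals.

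**Working it through.** **Inputs.** From Sample size estimation: p0 = 0.28, p1 = 0.40, power 80%, alpha 5% (two-sided assumed, in line with the 95% intervals), k = 0.15, c = 10 clusters per arm, 319 per cluster, total 8910, 10% loss. From the analysis section: k is a coefficient of variation.

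**Formula.** For a cluster-level comparison of proportions with m children per cluster in the denominator:

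c = 1 + (1.96 + 0.84)² × [p0(1−p0)/m + p1(1−p1)/m + k²(p0² + p1²)] / (p1−p0)²

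The fixed parts are:
- (1.96 + 0.84)² ≈ 7.849 with unrounded normal quantiles
- p0(1−p0) + p1(1−p1) = 0.2016 + 0.2400 = 0.4416
- k²(p0² + p1²) = 0.0225 × (0.0784 + 0.1600) = 0.005364
- (p1−p0)² = 0.0144

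**Attempt to reproduce the plan, m = 319.** c = 1 + 7.849 × (0.4416/319 + 0.005364)/0.0144 = 4.7, so 5 clusters per arm. With 10 per arm, power from the non-central t (18 df) is 99%. The plan's 20 clusters at 80% power are not reproduced. They would be at m = 319 only if k were about 0.25.

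**Solve for m at c = 10.** 9 × 0.0144/7.849 = 0.01651, and m = 0.4416/(0.01651 − 0.005364) = 39.6, so 40 per cluster. The non-central t gives 80.0% at m = 40. The stated clusters, power and k therefore fit about 40 children in the denominator.

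**Implied referral share.**
- At 319: 40/319 = 12.5%.
- At 8910/20 = 445.5: 40/445.5 = 9.0%.
- At 8910 × 0.9/20 = 401: 40/401 = 10.0%.

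**Power by assumed referral share** (10 clusters per arm, k = 0.15, non-central t with 18 df; the article gives no shares, so these are assumptions):

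| Control / intervention share | 319 per cluster | 401 to 445.5 per cluster |
|---|---|---|
| 5% / 5% | 51% | 58–62% |
| 10% / 10% | 74% | 80–83% |
| 12.5% / 12.5% | 80% | 85–88% |
| 20% / 20% | 90% | 93–94% |
| 5% / 15% | 66% | 73–76% |
| 10% / 20% | 82% | 87–89% |

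**If k is an intracluster correlation of 0.15.** The variance term becomes 0.4416 × [1 + (m−1) × 0.15]/m. At m = 319 this gives c = 37.7, so 38 clusters per arm. As m grows without limit, c tends to 1 + 7.849 × 0.4416 × 0.15/0.0144 = 37.1. Ten per arm cannot reach 80% at any referral share.

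**The total.** 319 × 20 = 6380. Adding 10% gives 6380 × 1.1 = 7018 or 6380/0.9 = 7089. Neither is 8910.

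**The case against.** The strongest reply is that 319 may itself be about 40 divided by an expected referral share near 12.5%, with that step left in the full protocol. This is possible, but the article does not say so. What it prints is a power statement in one unit and a target in another, so this is more than detail lost in condensing.

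Other objections stand and limit the point:

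- **A reader might infer that every cluster, including untrained control outlets, must reach 12.5%.** This is not so. The requirement is on the average. Shares of 10% in control and 20% in intervention give 82% power at 319 per cluster, with control below 12.5%.
- **A reader might take 12.5% as the single threshold.** It belongs to 319, which the abstract calls a minimum, and to equal shares. At the sizes implied by 8910 it is about 9–10%. As 8910 does not follow from 319, neither size is secure and a range is needed.
- **A reader might infer that recording stops at 319 children, or that the trial is underpowered.** The article supports neither. Registers are planned for about a year, Table 2 sets a 12-month evaluation period, and all referrals count. Achieved power depends on the referrals that accrue.
- **The Background remark on low referral is thin evidence.** It carries no figure and describes referral from lower to higher levels of care in Uganda and elsewhere in Africa. It makes a low share plausible and does not establish one.

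If the article loosely means 319 referred children, the design has more power than stated, which does no harm to the comparison. The sample size text would still be wrong.

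**Conclusion.** The point holds as a mismatch of units in a stated power calculation. With k = 0.15 as a coefficient of variation, a two-sided 5% test and 10 clusters per arm, 80% power corresponds to about 40 referred children with known outcome per cluster on average. It does not correspond to 319 of anything: 319 in the denominator would need about 5 clusters per arm.

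Read as consultations, the target gives 80% power only at an average referral share of about 12.5% (319 per cluster) or 9–10% (401–445.5 per cluster), if shares are equal in the two arms. Unequal shares move power either way, and the intervention trains its providers to refer, so equal shares are doubtful. The calculations also take referral counts as equal across clusters within an arm; uneven counts would lower power at the same average. If k is an intracluster correlation, the 80% fails at any share. The actual referral share is unknown from the article, so the size of any shortfall is unknown too.

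**What to change.** Restate the target in the unit of the primary outcome: on average about 40 referred children with known outcome per cluster, or about 45 referred before 10% loss (40/0.9 = 44.4). Say that k = 0.15 is the coefficient of variation, or redo the calculation if it is not. State the assumed referral share in each arm that links this to the number of sick children, and give power over a range of shares. Reconcile 319 × 20 = 6380 (7018–7089 with 10% added) with 8910. Monitor referrals per cluster, rather than consultations, over the 12 months of recording already planned.

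The cost is a rewritten sample size section and a different monitored count. The Study status section says 4 months of a one-year intervention have elapsed, so monitoring can still change. If k is a coefficient of variation, no clusters need to be added. The stated power may turn out less favourable than 80%.

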A cluster-level approach to the analysis will be used due to the small number of clusters per arm [17]. The proportion relating to this primary outcome will be calculated in each cluster. If the distribution of the proportions in each study arm is skewed a logarithmic transformation will be applied and the geometric mean proportions computed. To compare the intervention with the control arm point estimates based on these cluster summaries will be used to derive risk differences; using a weighted average of the cluster proportions, with weights proportional to the sample size for each cluster, since consultation rates differ between drug shops/private clinics and clusters. If the data have been log transformed, this will be the ratios of the geometric means. Corresponding 95 % confidence intervals will be computed assuming separate estimates of the variances in the two study arms, or if log transformed using an estimate of the pooled standard deviation of the log-transformed cluster summaries. The null hypothesis that there is no intervention effect will be tested using an unpaired *t*-test. Finally, an estimate of the coefficient of variation, *k*, will be provided. The overall mean proportion of sick children referred in the intervention arm, with 95 % confidence interval, will be computed using a random effects model to account for cluster sample. This analysis will be restricted to data from the treatment records of registered drug shop/private clinics enrolled in the intervention arm of the trial. A two-stage process will be carried out to adjust for covariates. At the first stage a regression model will be fitted incorporating the covariate(s) of interest, except the study arm. Expected values from this model will be compared with observed values by computing a residual, based on the difference between observed and expected, for each cluster. In the second stage, adjusted risk differences and 95 % CIs will be estimated as described above, replacing the cluster-level proportions with the covariate adjusted residuals. The covariates that will be adjusted for include balance criteria used in randomization at cluster level (primary endpoint at baseline); level of qualification, number of years working as a drug shop vendor/private clinic and/or health worker; age of sick child, education level of caretaker, and occupation of caretaker. A test for interaction will be carried out, and a 95 % confidence interval computed, using the methods of [18]. The above methods will also be used to analyse the other secondary outcomes; appropriate case management for malaria, pneumonia and diarrhea among children in the private sector and time between consultations at private outlets and uptake of referral at health facilities (referral facilities).

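### The sample-size paragraph cannot be rebuilt from its printed inputs: 8,910 does not follow from 319 children in 20 clusters with 10% loss, and neither reading of k = 0.15 returns 20 clusters at 80% power

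*Protocol article*

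**What the plan says.** Under Sample size estimation, the protocol article states: "The study will recruit 319 sick children per cluster". It goes on that "the total number of sick children to be recruited from all clusters will be 8910", a figure said to allow for 10% "loss to follow up and possible withdrawal of private outlets". No rate is attached to outlet withdrawal. The abstract gives the same numbers but treats 319 as a floor: "A minimum of 319 sick children per cluster".

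The other inputs are a rise in the primary outcome from 28% to 40%, 80% power, 5% significance and "a cluster correlation k, of 0.15; 20 clusters will be required", split 10 and 10 between the arms.

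Under Study outcomes and analytic methods, the symbol k has another meaning: "Finally, an estimate of the coefficient of variation", k, is to be reported. The same section makes referred children, not all sick children, the denominator of the primary outcome, and tests the effect with an unpaired t-test on cluster summaries.

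**The concern.** Two things do not fit together.

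- **The total.** The per-cluster number, the number of clusters and the only quantified loss rate do not multiply up to the printed total. A reader cannot tell which of 319 and 8,910 carries the design.
- **The clustering input.** An intracluster correlation and a between-cluster coefficient of variation are different quantities. At proportions of 28% to 40%, the value 0.15 means something very different under each name, so the label decides whether 20 clusters look far too few or more than enough.

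At stake is whether anyone can judge the trial as adequately sized, and against which number recruitment should be reported. A trial that reached 7,089 children would have met one printed target and fallen about 20% short of the other (7,089 / 8,910 = 0.796).

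**Working it through.** **Inputs.** From Sample size estimation: m = 319 per cluster, 20 clusters (c = 10 per arm), loss 10%, p0 = 0.28, p1 = 0.40, power 80%, alpha 5%, clustering input 0.15. From Study outcomes and analytic methods: t-test on cluster summaries (18 degrees of freedom). Assumed here: two-sided test, equal cluster sizes, the same clustering value in both arms.

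**1. The total**

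- Before loss: 319 x 20 = 6,380.
- After 10% loss: 6,380 x 1.1 = 7,018, or 6,380 / 0.9 = 7,089.
- Stated: 8,910, which is higher by 1,821 (26%) to 1,892 (27%).
- Overall loss implied by 8,910: 1 - 6,380 / 8,910 = 28.4%.

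Outlet withdrawal has no printed rate, so a range is needed. Applying it after the 10% loss, 6,380 / 0.9 / (1 - w):

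| Assumed withdrawal w | Total |
|---|---|
| 10% | 7,877 |
| 15% | 8,340 |
| 20% | 8,861 |
| 25% | 9,452 |

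About 20% comes close, but none of these round rates gives 8,910. Working back with no withdrawal, 8,910 / 1.1 / 20 = 405 and 8,910 x 0.9 / 20 = 401 per cluster. The first is exact: 405 x 20 x 1.10 = 8,910.

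**2. Reading 0.15 as an intracluster correlation**

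- Per arm without clustering: (1.96 + 0.84)² x (0.2016 + 0.24) / 0.12² = 240.7.
- Design effect: 1 + 318 x 0.15 = 48.7.
- Clusters per arm: 240.7 x 48.7 / 319 = 36.7, so 37. A pooled-variance formula gives 37.3, so 38.
- With unlimited children per cluster: 240.7 x 0.15 = 36.1, still 37 after rounding up.
- Power with 10 per arm: standard error √(0.4416 x 48.7 / 319 / 10) = 0.082, ratio 0.12 / 0.082 = 1.46. Power is 28.2% by t on 18 df, and 30% to 31% by normal approximation.

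**3. Reading 0.15 as a coefficient of variation**

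c = 1 + (1.96 + 0.84)² x [p0(1-p0)/m + p1(1-p1)/m + k²(p0² + p1²)] / (p1 - p0)²

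- With m = 319: the bracket is 0.00138 + 0.00536 = 0.00675, so c = 4.7, or 5 per arm.
- Power with 10 per arm: standard error √(0.00675 / 10) = 0.026, ratio 4.62. Power is 99.2% by t.
- Equivalent intracluster correlation, k²p/(1-p): 0.009 at 28% and 0.015 at 40%, some 10 to 17 times below 0.15.
- At m = 319, c = 10 would need k of about 0.25.

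**4. What would return 10 clusters per arm with k = 0.15?**

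The formula reduces to c = 3.92 + 240.7 / m. The article gives no number of referred children per cluster, so m is varied:

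| Analysed per cluster | Share of 319 | c per arm |
|---|---|---|
| 20 | 6% | 16.0 |
| 40 | 13% | 9.9 |
| 80 | 25% | 6.9 |
| 160 | 50% | 5.4 |
| 319 | 100% | 4.7 |

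Ten per arm appears at about 40 analysed children per cluster (39.6 for c = 10 exactly, or 12.4% of 319).

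**The case against.** **On the total.** The article names a second allowance, outlet withdrawal, and the abstract calls 319 a minimum. A floor per cluster and an inflated overall total need not be the same quantity, and a condensed article may leave the withdrawal rate to the full protocol. This stands in part: the article does not prove 8,910 wrong, only irreproducible. But the sample size section itself drops the word minimum, and a floor of 319 does not generate 8,910 either. It carries no weight that 8,910 / 20 = 445.5 is not a whole number, because the analysis section expects clusters of different size.

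**On k.** A reader who takes the printed label literally might infer that the trial has only 28% power. The documents do not support that. The analysis section uses the same symbol for a coefficient of variation, and on that reading power at 319 per cluster is about 99%. The opposite inference, that the design is safely oversized, is not supported either: the 99% assumes that all 319 children count towards the primary outcome, whereas only referred children do.

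**On consequences.** Recruitment runs by calendar period (October 2015 to September 2016 in Table 2), the article gives no stopping rule tied to 8,910, and the total errs upward. This stands, and it lowers the severity.

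**Conclusion.** The point holds as a failure of the printed calculation. The total exceeds what 319, 20 clusters and 10% loss give by 26% to 27%, and the difference rests on an unstated withdrawal rate of about 20% or on a different base of 401 to 405 per cluster. The clustering input carries two names, and under neither does the paragraph return 20 clusters at 80% power with 319 per cluster: about 37 per arm under one and 5 per arm under the other, against the planned 10.

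That k was meant as a coefficient of variation is an inference from the shared symbol and from the formula giving 10 per arm at about 40 analysed children. That these 40 are the expected referrals among 319 sick children is a further inference; the article gives no referral fraction. The figures rest on a two-sided 5% test, equal cluster sizes and a common clustering value in both arms.

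Severity is moderate: the primary sample-size statement needs correcting, but nothing here shows that the trial is too small.

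**What to change.** Rewrite the sample size paragraph and the matching abstract sentence as one reproducible set:

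1. Name k = 0.15 as the between-cluster coefficient of variation, or state the intracluster correlation actually used.
2. Give the number of referred children per cluster that enters the formula, and the assumed referral fraction that links it to sick children.
3. Restate the number of clusters, or the power, that these inputs give. Renaming k while keeping 319 as the analysed number would still not return 20 clusters at 80% power.
4. State the outlet-withdrawal rate if one was used.
5. Reconcile the per-cluster number with the total: 7,089 if 319 and 10% loss alone stand, or 401 to 405 per cluster before loss if 8,910 stands with no withdrawal allowance.

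The cost is a text correction. It changes no clusters, procedures or recruitment period.

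### The sample-size statement does not follow from its own inputs: with 319 children analysed per cluster, no reading of k = 0.15 gives 80% power with 20 clusters

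*Protocol article*

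**What the plan says.** The Sample size estimation section states the cluster size: "The study will recruit 319 sick children per cluster". It assumes that "the intervention will increase the primary outcome from 28 to 40" per cent, and concludes "at a study power of 80 %, 5 % level of significance and a cluster correlation k, of 0.15; 20 clusters will be required", split 10 and 10.

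The section on study outcomes and analytic methods sets the analysis. Proportions are calculated per cluster, and "The null hypothesis that there is no intervention effect will be tested using an unpaired *t*-test". It also says what k denotes: "Finally, an estimate of the coefficient of variation, *k*, will be provided". The same section limits the denominator of the primary outcome to children who were referred from a private outlet. The sample-size section counts sick children and gives no referral fraction.

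**The concern.** A reader who puts the printed inputs into the standard formula for comparing cluster proportions does not get the printed result. The gap is too large for rounding. On one reading of k the trial has twice the clusters it needs; on the other it has about a quarter of them.

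k is also the dominant input. At 319 per cluster and k = 0.15 as a coefficient of variation, it supplies about 80% of the variance (0.00536 of 0.00675). Without knowing k, its definition and the number of children analysed, nobody can say what power the trial has or how to read a null result. The estimate of k promised at the end of the trial would also be compared with a planning value whose meaning is unclear.

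**Working it through.** **Inputs.** From Sample size estimation: p0 = 0.28, p1 = 0.40, m = 319 per cluster, c = 10 clusters per arm, 5% significance, 80% power, k = 0.15. From the analysis section: k is a coefficient of variation, and the test is an unpaired t-test on cluster summaries. Assumed: two-sided test, because sidedness is not stated.

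**Formula (unmatched clusters, proportions).** With V the sum over the two arms of the variance of one cluster proportion:

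- V = [p0(1−p0) + p1(1−p1)]/m + k²(p0² + p1²)
- c = 1 + (1.96 + 0.8416)² × V/(p1−p0)²
- power = Φ( √[(c−1)(p1−p0)²/V] − 1.96 )

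Constants: p0(1−p0) + p1(1−p1) = 0.2016 + 0.2400 = 0.4416; p0² + p1² = 0.0784 + 0.1600 = 0.2384; (p1−p0)² = 0.0144; (2.8016)² = 7.849; 7.849/0.0144 = 545.1.

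**Step 1: k = 0.15 as a coefficient of variation, m = 319.**

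- V = 0.4416/319 + 0.0225 × 0.2384 = 0.00138 + 0.00536 = 0.00675
- c = 1 + 545.1 × 0.00675 = 4.68, so 5 per arm (10 in total), not 20
- power at 10 per arm = Φ(√[9 × 0.0144/0.00675] − 1.96) = Φ(2.42) = 99.2%

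A noncentral t with 18 df also gives 99.2%. A one-sided test without the added cluster gives 99.7%. Taking m from 287 (319 less 10%) to 445.5 (8910/20) gives 99.1% to 99.5%. The 80% is not reproduced.

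**Step 2: 0.15 as an intracluster correlation, m = 319.**

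- Design effect = 1 + 318 × 0.15 = 48.7
- V = 0.4416 × 48.7/319 = 0.0674
- c = 1 + 545.1 × 0.0674 = 37.75, so 38 per arm
- power at 10 per arm = Φ(√[0.1296/0.0674] − 1.96) = 28%

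Read as a between-cluster standard deviation, 0.15 gives c = 26.3 and about 39% power.

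**Step 3: what would restore the printed result?**

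*A different k.* At k = 0.25 and m = 319, V = 0.00138 + 0.01490 = 0.01628, c = 9.88 and power is about 80%.

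*A different m.* Keep k = 0.15 as a coefficient of variation and 10 per arm, and let m be the referred children per cluster. The fractions of 319 are assumptions.

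| Assumed fraction referred | Referred per cluster | Clusters per arm for 80% | Power at 10 per arm |
|---|---|---|---|
| 5% | 16 | 19.0 | 51% |
| 10% | 32 | 11.5 | 74% |
| 12.5% | 40 | 9.9 | 80% |
| 20% | 64 | 7.7 | 90% |
| 100% | 319 | 4.7 | 99% |

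Both changes return 10 per arm at about 80%, so the arithmetic cannot tell them apart.

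**The case against.** The best defence is that nothing is wrong with k or the power. The figure of 319 counts sick children, while the primary outcome is measured only in those referred. If about one in eight is referred, some 40 per cluster are analysed, and k = 0.15, 80% power, 20 clusters and 319 recruited all agree. This stands as a possible explanation, and it rules out the claim that either k or the power must be misprinted. It does not rescue the text. The section presents 319 as resting on the listed assumptions, and no referral fraction is among them. Nor is this merely detail left to a fuller document: a printed result disagrees with the inputs printed beside it.

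Three stronger readings are tempting, and the article does not support them:

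- **The trial really has 99% power.** That holds only if k is a coefficient of variation of 0.15 and all 319 children per cluster enter the primary denominator. With 16 or 32 referred per cluster, power is about 51% or 74%.
- **The value used was k = 0.25.** The fit is suggestive only, because k was solved from the cluster count. At k = 0.25 the formula rounds up to 10 per arm for any m of about 274 or more (c tends to 1 + 545.1 × 0.0149 = 9.12 as m grows), so 319 is not singled out. The value 0.25 appears nowhere in the article.
- **The trial has only 28% power.** That takes "a cluster correlation k, of 0.15" as an intracluster correlation. The wording allows it, but the analysis section uses the same symbol for the coefficient of variation, which makes that the better reading.

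The per-cluster figure is in doubt for another reason: 319 × 20 = 6380, or 7089 after dividing by 0.9, not the stated 8910. Step 1 shows that this hardly moves the power at k = 0.15, but it is a further reason not to treat 319 as the one secure input.

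**Conclusion.** The statement is wrong as written. With 319 analysed per cluster and a two-sided 5% test (assumed), 10 clusters per arm give about 99% power if 0.15 is a coefficient of variation and about 28% if it is an intracluster correlation. The corresponding requirements for 80% power are about 5 and about 38 clusters per arm, against the 10 stated.

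The cause cannot be settled from the article. The value of k, its definition, or the number of children analysed per cluster could each be the faulty input, and the actual power could lie above or below 80%. The error is one of reporting and justification. It does not by itself show that the design is too large or too small.

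**What to change.** Return to the original calculation and correct the Sample size estimation section:

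1. Call k the coefficient of variation, or an intracluster correlation if that was used, and print the value used.
2. State whether 319 is sick children or referred children, and the referral fraction assumed.
3. Restate the power of 10 clusters per arm for the number of referred children per cluster expected in the primary analysis.
4. If the recomputed number of clusters is not 20, replace the claim that 20 are required.

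The 99% figure should not be printed as the trial's power unless all 319 per cluster belong to the primary denominator.

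The cost is one recomputation and a corrected paragraph, with no change to clusters, enrolment or analysis. This remains feasible with the intervention already under way. The downside is that the restated power may be less favourable than 80%.
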